# Right median nerve electrical stimulation for acute traumatic coma (the Asia Coma Electrical Stimulation trial): study protocol for a randomised controlled trial

**DOI:** 10.1186/s13063-017-2045-x

**Published:** 2017-07-10

**Keywords:** Traumatic brain injury, Comatose patient, Right median nerve electrical stimulation

## Abstract

**Background:**

Traumatic brain injury (TBI) has become the most common cause of death and disability in persons between 15 and 30 years of age, and about 10–15% of patients affected by TBI will end up in a coma. Coma caused by TBI presents a significant challenge to neuroscientists. Right median nerve electrical stimulation has been reported as a simple, inexpensive, non-invasive technique to speed recovery and improve outcomes for traumatic comatose patients.

**Methods/design:**

This multicentre, prospective, randomised (1:1) controlled trial aims to demonstrate the efficacy and safety of electrical right median nerve stimulation (RMNS) in both accelerating emergence from coma and promoting long-term outcomes. This trial aims to enrol 380 TBI comatose patients to partake in either an electrical stimulation group or a non-stimulation group. Patients assigned to the stimulation group will receive RMNS in addition to standard treatment at an amplitude of 15–20 mA with a pulse width of 300 μs at 40 Hz ON for 20 s and OFF for 40 s. The electrical treatment will last for 8 h per day for 2 weeks. The primary endpoint will be the percentage of patients regaining consciousness 6 months after injury. The secondary endpoints will be Extended Glasgow Outcome Scale, Coma Recovery Scale-Revised and Disability Rating Scale scores at 28 days, 3 months and 6 months after injury; Glasgow Coma Scale, Glasgow Coma Scale Motor Part and Full Outline of Unresponsiveness scale scores on day 1 and day 7 after enrolment and 28 days, 3 months and 6 months after injury; duration of unconsciousness and mechanical ventilation; length of intensive care unit and hospital stays; and incidence of adverse events.

**Discussion:**

Right median nerve electrical stimulation has been used as a safe, inexpensive, non-invasive therapy for neuroresuscitation of coma patients for more than two decades, yet no trial has robustly proven the efficacy and safety of this treatment. The Asia Coma Electrical Stimulation (ACES) trial has the following novel features compared with other major RMNS trials: (1) the ACES trial is an Asian multicentre randomised controlled trial; (2) RMNS therapy starts at an early stage 7–14 days after the injury; and (3) various assessment scales are used to evaluate the condition of patients. We hope the ACES trial will lead to optimal use of right median nerve electrical treatment.

**Trial registration:**

ClinicalTrials.gov, NCT02645578. Registered on 23 December 2015.

**Electronic supplementary material:**

The online version of this article (doi:10.1186/s13063-017-2045-x) contains supplementary material, which is available to authorized users.

## Background

The incidence of traumatic brain injury (TBI), which is the most common cause of death and disability in persons between 15 and 30 years of age, has increased as a result of heavy traffic [1, 2]. Approximately 10–15% of patients with severe TBI end up in a coma or vegetative state [1, 3, 4]. It is now believed that coma is a self-limiting state that typically evolves within 2–4 weeks into a vegetative state (VS), minimally conscious state (MCS), or conscious state (CS) [5]. A VS is a condition of wakeful unconsciousness in which patients can open their eyes spontaneously but cannot understand, communicate or behave purposefully. An MCS is a condition of severely altered consciousness characterised by minimal but definite behavioural evidence of self-awareness or environmental awareness. The examiner may elicit clear evidence of volitional behaviour on one examination, but fail to do so during a subsequent examination conducted hours or even minutes later [6, 7]. Coma and its unfavourable successions, VS and MCS, have become a heavy burden for families and society.

Neuroscientists are working on how to speed recovery and improve the functional outcomes and prognosis of these patients. Treatments including pharmacological interventions, right median nerve stimulation (RMNS), sensory stimulation, dorsal column stimulation, transcranial magnetic stimulation, deep brain stimulation and hyperbaric oxygen therapy have all been used to better achieve rehabilitation goals [3, 8–12]. No treatment has been proven robustly to alter the pace of recovery or improve the neurological outcomes of comatose patients following TBI.

As a simple, inexpensive, non-invasive technique, RMNS for coma arousal has a history of more than two decades. The application of electrical current to the extremities to treat central nervous system injury was first introduced in 1972 at the University of Virginia [13]. Radio-linked electrodes were surgically implanted on the bilateral femoral and sciatic nerves of a paraplegic patient to produce a semblance of walking using an external switch. Unexpectedly, in the mid-1980s researchers at Duke Biomedical Engineering not only noted a significant improvement in motor responses to electrical pulses in the stimulated arm of a quadriplegic subject, but also discovered a crossover effect of improvement in the strength of the proximal muscles of the unstimulated arm [14, 15]. This observation of intracerebral transfer led to the development of median nerve electrical stimulation for coma arousal. The first article about median nerve electrical stimulation for acute coma was published in 1999 [16]. Since then, RMNS has drawn increasing attention from many intensivists, rehabilitationists and clinical researchers [3, 5, 14, 17–23].

Among the articles published on RMNS, three randomised trials give some clues about the efficacy of this treatment. In the first randomised, double-blind study, a group of six comatose patients with TBI were randomised to receive RMNS treatment or sham stimulation. The RMNS group recovered more quickly, with a shorter intensive care unit (ICU) stay and improved Glasgow Coma Scale (GCS) and Glasgow Outcome Scale (GOS) scores 1 month after the injury [16]. In a double-blind randomised controlled trial with six RMNS-treated patients and four controls, the RMNS group emerged from coma 2 days earlier and scored higher in the Functional Independence Measure/Functional Assessment Measure (FIM/FAM) 3 months post injury [19]. In a third double-blind randomised controlled trial conducted by Lei and colleagues, 437 comatose patients with severe TBI were enrolled 2 weeks after their injury and assigned to the RMNS group or the control group according to their date of birth. The RMNS-treated patients had a more rapid increase in mean GCS, a significantly higher proportion of them regained consciousness and a lower proportion ended in VS. For those patients who regained consciousness, the FIM score was higher among the RMNS group [24].

Non-randomised controlled trial studies and reviews, although not as convincing, also indicate that RMNS may play a role in the emergence from coma following severe brain injury. For example, Liu and colleagues used RMNS on six comatose patients for 3 months. Four patients regained consciousness within 35 days, and brain perfusion increased in all six cases assessed by single-photon emission computed tomography (SPECT) scans after stimulation [20]. A review by Cooper and colleagues concluded that RMNS is a promising therapy for the neuroresuscitation of comatose patients, and time in the ICU may be shortened and the quality of the final outcome enhanced when the stimulation is applied early in the coma [18].

The trials selected had limitations due to the small number of cases analysed in most studies, inappropriate methods of randomisation in some cases, the diversity in coma length and coma severity, the heterogeneity of outcome measures, the different timing of intervention and follow-up and the lack of multicentre studies. We designed the ACES trial with an adequate sample size and a standardised protocol to obtain convincing evidence about the efficacy and safety of RMNS in both accelerating emergence from coma and promoting long-term outcomes.

## Methods/design

### Overview

A Standard Protocol Items: Recommendations for Interventional Trials (SPIRIT) checklist is available online for this manuscript (Additional file 1).

The Asia Coma Electrical Stimulation (ACES) trial is a prospective, Asian multicentre randomised controlled trial designed to examine the efficacy and safety of 2-week long right median nerve electrical stimulation in patients suffering from acute traumatic coma. Patients enrolled in the trial are randomly assigned to the stimulation group or the non-stimulation group. The primary endpoint, 6 months after injury, is the level of consciousness: VS, MCS, or CS (Fig. 1). Its design and the final report will follow the Consolidated Standards of Reporting Trials (CONSORT) statement as well as its extension to non-pharmacological interventions. The trial schedule is shown in Fig. 2.

**Fig. 1 Fig1:**
[figure not shown]
Overview of the flow of participants through the trial

**Fig. 2 Fig2:**
[figure not shown]
Schedule of enrolment, interventions and assessments. *GCS* Glasgow Coma Scale, *CT* computed tomography, *GMS* Glasgow Coma Scale Motor Part, *FOUR* Full Outline of Unresponsiveness (scale), *CRS-R* Coma Recovery Scale-Revised, *DRS* Disability Rating Scale, *GOSE* Extended Glasgow Outcome Scale

### Study settings and population

A total of 380 patients will be recruited from 16 large, experienced, specialised neurosurgical centres across Asia: (1) Shanghai Renji Hospital; (2) Guangzhou General Hospital of Guangzhou Military Region; (3) the People’s Hospital of Shaoxin, Zhejiang; (4) the 98 Hospital of the People’s Liberation Army; (5) the Second People’s Hospital of Nanning, Guangxi; (6) the Central People’s Hospital of Tengzhou, Shandong; (7) Harrison International Peace Hospital of Hengshui, Hebei; (8) the 421 Hospital of the People’s Liberation Army; (9) Jiangning Hospital of Nanjing, Jiangsu; (10) the First People’s Hospital of Yulin, Guangxi; (11) the First People’s Hospital of Huaian, Jiangsu; (12) the People’s Hospital of Hunan; (13) the People’s Hospital of Pingyang, Zhejiang; (14) the Second People’s Hospital of Tianshui, Gansu; (15) the Fifth People’s Hospital of Zhengzhou University; (16) General Hospital of Beijing Military Region.

### Inclusion and exclusion criteria for the trial

Patients who meet the following criteria will be deemed eligible for the trial: (1) admitted to the hospital due to closed TBI 7 to 14 days previously; (2) GCS score of 4–8 or GMS below 5 on admission; and (3) aged 18–65 years old.

Those who meet the following criteria will be excluded from the trial: (1) vital signs not stable; (2) admitted to hospital due to penetrating cranial injury; (3) a confirmed history of epilepsy before enrolment or during the time of hospitalisation; (4) severe cardiac arrhythmia or pacemaker implanted; (5) pregnancy; and (6) no consent form.

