### Randomisation and allocation concealment

Participants at each site will be randomly assigned in a ratio of 1:1, stratified by study centre, to the stimulation group or the non-stimulation group, using a block-randomisation scheme. The whole randomisation procedure will be carried out by independent statisticians who are not involved in the determination of the final result. The trial secretary will place the computer-generated randomisation sequence and treatment assignment together into opaque envelopes and seal and mail these envelopes to each participating centre. After each patient is stabilised, assessed and identified as possibly meeting the criteria, a study physician at each local centre will do the group assignment by opening sequentially numbered envelopes.

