### Treatment protocol

After being admitted to the hospital, all patients will be assessed and receive standard treatment (including surgery, if necessary) in the neurology ICU in accordance with the current guidelines [25]. Those who meet the criteria and whose representative has signed an informed consent form will be enrolled in the trial and be randomly assigned to the stimulation or non-stimulation group according to the procedure mentioned above.

The patients in the stimulation group will receive RMNS in addition to standard treatment. The electrical treatment will be delivered via a pair of lubricated 1-inch square rubber surface electrodes pasted 1 inch apart on the volar aspect of the right distal forearm over the median nerve. An electrical neuromuscular stimulator (Verity Medical Ltd., Braishfield, UK) will supply trains of asymmetric biphasic pluses at an amplitude of 15–20 mA (as tolerated) with a pulse width of 300 μs at 40 Hz ON for 20 s and OFF for 40 s, which has been proven to be well tolerated without causing pain or skin irritation. The electrical stimulation treatment will last for 8 h per day for 2 weeks. Patients assigned to the control group will continue to receive the previous standard treatment without electrical stimulation. During treatment, all patients will receive intensive care to prevent hypotension, hypoxia, intracranial hypertension and disturbance of homeostasis.

In addition to vital signs and general data, some additional data from the case report forms (CRFs) will be assessed at the beginning of the trial and during treatment. Once enrolled in the trial, the GCS, Glasgow Coma Scale Motor Part (GMS), Full Outline of Unresponsiveness (FOUR) scale, Coma Recovery Scale-Revised (CRS-R) and Disability Rating Scale (DRS) scores of each patient will be collected.

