### Data collection and follow-up

General baseline information will be collected about patients when they are sent to the emergency room and will include the following: demographics, time of admission, cause of injury, whether accompanied by multiple trauma, injury severity score, initial GCS score, initial intracranial computed tomography (CT) data including Marshall score and whether complicated by subarachnoid haemorrhage, pupillary light reflex or the need of craniotomy.

After 7–14 days of standard treatment, when the patient’s condition is stable and once he/she is enrolled and randomised, additional data will be collected, including vital signs such as blood pressure, heart rate, respiratory rate and oxygen saturation, pupillary light reflex and GCS, FOUR, CRS-R and DRS scores.

Patients in both the RMNS group and the sham group will be evaluated via GCS and FOUR scores at day 1 and day 7 of the treatment. Whether or not the coma patient regains consciousness and the date will be recorded in the CRF. Any complications will also be observed and recorded during the treatment.

Outcome assessment will be performed using the GCS, FOUR, CRS-R, DRS and GOSE at 1, 3 and 6 months. Complications during follow-up will also be assessed. If the patient is still in the hospital, the investigator may visit the patient on the ward to go through the evaluation. If the patient has been discharged, his or her legal representative will be told to come back in due time for assessment after leaving the hospital. If the patient does not arrive, the investigator will try to contact the patient or the family members by telephone. Other possible methods may also be used to explain the situation and complete the outcome assessment. If all attempts fail, no further contact will be made, and the patient will be recorded as lost to follow-up. Any death occurring either in or out of the hospital will be recorded and possible causes explored.

All the data will be collected by independent investigators who are blind to the patient’s allocation. Each local study centre will assign a specific investigator at the beginning of the trial. This investigator will be excluded throughout treatment of all the participants unless asked to do the assessment by clinicians. During the 2 weeks of RMNS treatment, the investigators will be asked to collect the data during the interval of 8-h RMNS treatment per day so as to eliminate any chance of disclosing the allocation.

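### The level-of-consciousness criterion applies on admission, 7 to 14 days before randomisation, so the written rule does not require patients to be unconscious when randomised

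*Protocol article*

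**What the plan says.** All references are to the Protocol article.

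- **Inclusion and exclusion criteria for the trial.** This is the only eligibility list. The timing criterion is "admitted to the hospital due to closed TBI 7 to 14 days previously" and the consciousness criterion is "GCS score of 4–8 or GMS below 5 on admission". No inclusion or exclusion item mentions level of consciousness at enrolment or randomisation.
- **Randomisation and allocation concealment.** The step before allocation reads "identified as possibly meeting the criteria, a study physician at each local centre will do the group assignment by opening sequentially numbered envelopes".
- **Treatment protocol.** The order of events is given differently: "Those who meet the criteria and whose representative has signed an informed consent form will be enrolled in the trial and be randomly assigned".
- **Data collection and follow-up.** An initial GCS is taken in the emergency room. A second set of scores (GCS, FOUR, CRS-R, DRS) comes later: "After 7–14 days of standard treatment, when the patient’s condition is stable and once he/she is enrolled and randomised, additional data will be collected". Neither set is made a condition of entry.
- **Title, Abstract, Overview and Ethics issues.** The population is described as comatose, and the consent text presumes that patients cannot consent for themselves.
- **Background and Sample size justification.** The planning rates of 59.8% and 46.2% come from an earlier randomised trial whose patients are described as comatose and as enrolled two weeks after injury.

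**The concern.** The primary endpoint is the proportion who have regained consciousness at 6 months. That presupposes a patient who is unconscious at the start. The criterion that should secure this is fixed at hospital admission, a week or two before allocation. The Background itself says that coma is a passing state, usually resolving into another state over two to four weeks, and that a conscious state is one of the possible results. Some change between admission and randomisation is therefore foreseeable.

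A patient who has woken by the time of allocation has nothing left to regain, but would most likely be scored as a success whichever arm is drawn. Such patients carry no information about the treatment effect on this endpoint and pull the two rates together. They also make the enrolled population differ from the one that supplied the planning rates.

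A second looseness sits at the same point in the process. If the envelope may be opened for someone who only possibly qualifies, some patients can be found ineligible after their allocation is known. This strains the commitment under Statistical analysis to include everyone randomised.

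**Working it through.** **Inputs from the documents.** Rates p1 = 0.598 and p2 = 0.462 (difference 0.136), α = 0.05, power 0.80, stated N = 334, and 380 in total (190 per group) with a stated 84% power, all from Sample size justification. Two-sided 0.05 is from Statistical analysis. Allocation is 1:1.

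**Input not in the documents.** f, the share of randomised patients already conscious. It is assumed here, over 5% to 20%.

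**Step 1: reproduce the plan's figure.** Per group, with p̄ = (p1 + p2)/2 = 0.530:

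n = [z_α √(2p̄(1−p̄)) + z_β √(p1(1−p1) + p2(1−p2))]² / (p1−p2)²

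The two roots are √0.4982 = 0.7058 and √0.4890 = 0.6993.

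- One-sided: (1.645 × 0.7058 + 0.842 × 0.6993)² / 0.0185 gives 166 per group, 332 in total. Power at 190 per group is 84.6%. These agree closely with the stated 334 and 84%.
- Two-sided: z_α = 1.960 gives 211 per group, 422 in total. Power at 190 per group is 75.9%.

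The stated figures thus match a one-sided test, while the analysis section specifies a two-sided one. That is a separate matter. Both versions are carried below so that it is not confused with the present point.

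**Step 2: dilution model.** Suppose a share f is already conscious at randomisation and conscious at 6 months in both arms. Then:

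- p1′ = f + (1−f) × 0.598
- p2′ = f + (1−f) × 0.462
- p1′ − p2′ = (1−f) × 0.136

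Worked case, f = 10%: p1′ = 0.10 + 0.90 × 0.598 = 0.638, p2′ = 0.10 + 0.90 × 0.462 = 0.516, difference 0.122.

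Power = Φ{[√190 × (p1′−p2′) − z_α √(2p̄′(1−p̄′))] / √(p1′(1−p1′) + p2′(1−p2′))}

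| f (assumed) | Difference, points | Power at 190 per group, one-sided | two-sided | Total N for 80%, one-sided | two-sided |
|---|---|---|---|---|---|
| 0 | 13.6 | 84.6% | 75.9% | 332 | 422 |
| 5% | 12.9 | 81.5% | 71.8% | 366 | 464 |
| 10% | 12.2 | 78.1% | 67.7% | 402 | 510 |
| 20% | 10.9 | 70.8% | 59.1% | 490 | 620 |

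**Step 3: sensitivity.** If 95% rather than all of the already-conscious patients are conscious at 6 months, equally in both arms, the differences are unchanged. Two-sided power is then 67.5% at f = 10% and 58.7% at f = 20%. The result depends on f and hardly at all on this second assumption.

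**Step 4: the two allocation passages side by side.** The randomisation section asks for possible eligibility, does not mention consent, and then opens the envelope. The treatment section asks for criteria met and consent signed, and then randomises by the procedure just described. Both cannot be the rule. The assessment mentioned in the randomisation section does not close the gap on consciousness either, because it refers back to the same criteria, which look to admission.

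**The case against.** The best reply is intent. The title, Abstract and Overview all speak of comatose patients, the consent text assumes incapacity, and an endpoint of regaining consciousness implies its absence at entry. The Background puts the usual evolution of coma at two to four weeks, so allocation at days 7 to 14 falls before or at the start of that window, and two of the three states it names fall short of full consciousness. The endpoint's definition of consciousness is demanding, so leaving coma is not the same as meeting it. All of this stands. It makes the fault one of wording and suggests that f may be small. It does not supply a criterion, and sixteen centres screen against the criteria.

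A reader might infer more than the documents support:

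- *That awake patients are being enrolled and the endpoint is diluted.* The text permits this but does not show it. Sites may in practice enrol only comatose patients.
- *That no score exists before allocation.* The randomisation section has patients assessed first without naming the scales, and the schedule figure is not shown.
- *That the epilepsy exclusion, "a confirmed history of epilepsy before enrolment or during the time of hospitalisation", removes patients who have a seizure after randomisation.* An exclusion list governs entry. Study endpoint counts seizures as adverse events to 6 months, and Statistical analysis keeps everyone randomised.
- *That the motor-score alternative contradicts the 4–8 range.* It is joined by an or, widens entry, and may be deliberate.

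**Conclusion.** The point holds as a defect in the operative criterion. The stated rule does not require unconsciousness at randomisation, and it disagrees with the population the article describes and with the one behind its planning rates. If already-conscious patients do enter, the direction of the effect is clear: the difference shrinks by (1 − f).

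The size is not established, because f is assumed. Over 5% to 20% the loss of power at 190 per group is about 3 to 14 percentage points one-sided (84.6 − 81.5 and 84.6 − 70.8) and about 4 to 17 two-sided (75.9 − 71.8 and 75.9 − 59.1). These figures take every randomised patient as evaluable and take the already-conscious to fare equally in both arms. The gap between 84.6% and 75.9% at f = 0 belongs to the one-sided versus two-sided question and should not be charged to this point.

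The conflict over when the envelope is opened is real but small in wording. The whole should be fixed. It does not by itself undermine the trial.

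**What to change.** 1. In the eligibility list, apply the existing GCS/GMS criterion at a documented assessment at enrolment as well as on admission.
2. In Data collection and follow-up, have the enrolment GCS, FOUR, CRS-R and DRS, which are already planned, recorded before the envelope is opened.
3. In Randomisation and allocation concealment, replace possible eligibility with confirmed eligibility and signed consent, so that it agrees with Treatment protocol.

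The cost is amendment wording, with no new measurements. Patients who wake before enrolment would no longer be eligible, so recruitment may be somewhat slower, by an amount that depends on the same unknown f. The article says recruitment is under way. Anyone already randomised should stay in the analysis, since removing them afterwards would breach the intention-to-treat rule.
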